**Type of Study:**

- ☐ Basic Research ☒ Clinical Research ☐ Database Review (non-medical records)  
☐ Questionnaire / Survey / Interview / Focus Group ☐ Tissue Banking  
☐ Emergency Research  
☐ Others, please specify \_\_\_\_\_

**Target Research Subjects are:**

- ☐ Healthy Adults ☐ Minors (under 21) ☐ Pregnant Women ☐ Outpatients ☐ Prisoners  
☒ Elderly ☐ Deceased  
☐ Adults or minors who lack mental capacity - *please fill in section 4.2.*  
☐ Minors who lack sufficient understanding and intelligence to give consent - *please fill in section 4.2.*

**Research Subjects Will Be:**

- ☒ Reimbursed \$30 ☐ Not reimbursed ☐ Others - please specify: \_\_\_\_\_

**Has this research been rejected by any IRB / REC / DERCs?**

- ☒ No ☐ Yes If yes, please provide details: \_\_\_\_\_

**This research is also submitted to or approved by:**

☐ NHG Domain-Specific Review Board (DSRB) A / B / C / D / E / F

☐ SingHealth Centralized IRB (CIRB) A / B / C / D / E / F

☐ Others, please specify \_\_\_\_\_

☒ **Not Applicable**

**HBR Checklist**

**This Research Involves:**

(N.B. If none of the boxes here are ticked, you are advised to use the SBER forms for your application)

**Study Objectives/Processes:**

- ☒ The prevention, prognostication, diagnosis or alleviation of any disease, disorder or injury affecting the human body.
- ☐ The restoration, maintenance or promotion of the aesthetic appearance of human individuals through clinical procedures or techniques.
- ☐ The performance or endurance of human individuals.
- ☐ The research involves any of the following:
  - ☐ Human gametes or human embryos.
  - ☐ Cytoplasmic hybrid embryos.
  - ☐ Introduction of any human-animal combination embryo into an animal or a human, or any entity created as a result of this process.

**OFFICIAL USE ONLY**

NUS-IRB Application Form (for HBR)

(IRB-FORM-H02)

- ☐ Introduction of human stem cells (including induced pluripotent stem cells) or human neural cells into an animal at any stage of development (including a prenatal animal foetus or animal embryo), or any entity created as a result of this process.

**Intervention:** *(including any willful act or omission, that has a physical, mental or physiological effect (whether temporary or permanent) on the body of the individual)*

☒ Yes ☐ No

**Biological Samples:**

- ☐ Human biological materials (excluding human tissues) – identifiable / coded.
- ☐ Human biological materials (excluding human tissues) – anonymised.
- ☐ Human tissues – identifiable / coded.
- ☐ Human tissues – anonymised.

**Health Information:**

- ☒ Health information (not obtained from medical records) – identifiable / coded.
- ☐ Health information (not obtained from medical records) – anonymised.
- ☐ Medical records/clinical data from healthcare institutions, e.g. clinics and hospitals (including MRI, CT scans, blood test and etc.).

Please specify source: \_\_\_\_\_

The records are: ☐ Identifiable / coded to the research team.

☐ Anonymised to the research team.

**OFFICIAL USE ONLY**

NUS-IRB Application Form (for HBR)

(IRB-FORM-H02)

**OFFICIAL USE ONLY**

NUS-IRB Application Form (for HBR)

(IRB-FORM-H02)

Page 5 of 25

Version No. 1, dated 15/05/2020

Version 2, 1 Jul 2019

**OFFICIAL USE ONLY**

NUS-IRB Application Form (for HBR)

(IRB-FORM-H02)

**\*\* IMPORTANT - Please complete ALL sections.**

## **V. ABSTRACT OF RESEARCH PROPOSAL**

***In no more than 300 words***, describe concisely the specific aims, hypotheses, methodology and approach of the application, indicating where appropriate the application's importance to science or medicine. The abstract must be self-contained so that it can serve as a succinct and accurate description of the application when separated from it. Please use lay terms and spell out all acronyms when they are used the first time. If it is not possible to use lay terms, the technical and medical terms should be explained in simple language.

Our study aims to explore the role of technology -- in the form of smart watches and mobile phone application -- in physical activity enhancement on cognitive frailty outcomes. Cognitive frailty is defined here as having both physical frailty and cognitive impairment but does not satisfy criteria for Major Neurocognitive Disorder. We postulate that for pre-frail older adults with mild cognitive impairment, such technology will help increase engagement in physical activity with subsequent improvement in cognitive and physical outcomes at follow up. This is with the aim of preventing this particular group from deteriorating to cognitive frailty because of the accompanying increased risk for adverse outcomes and morbidity.

This pilot study will be a randomized control trial with 2 treatment arms. Assessments will be done prior to and following the intervention period. During the period of intervention, the wearable will act as a tracking device and will be paired with a mobile application to issue prompts to the participant when necessary. The independent variable explored in the study is the use of the wearable while the levels of physical and cognitive improvements are the dependent measures. These will be tracked at baseline, 3 months and 6 months. Additionally, the mediating variable measured is the levels of physical activity to ensure that the proposed outcomes are affected through an increased level of physical activity encouraged by the use of the device.

If innovations like technology and the role of self-management proves efficacious, the future of healthcare in the context of a rapidly aging population will be more sustainable. Furthermore, this supporting role of technology in positive behavioral modification amongst older adults can have a multitude of applications in subsequent healthcare interventions.

## **VI. PROTOCOL DETAILS**

Organise details of the research protocol under the following headings (in no more than 7 pages).

### **1. Specific Aims:**

**1.1** *State concisely and realistically the purpose of the biomedical research, what the research described in this application is intended to accomplish and/or what hypothesis is to be tested.*

This study intends to determine if smart watches and mobile phone application prompts can complement physical activity as a preventive intervention by motivating them to exercise, so as to improve their physical and cognitive outcomes.

#### **OFFICIAL USE ONLY**

NUS-IRB Application Form (for HBR)

(IRB-FORM-H02)

We hypothesize that technology will help increase engagement in physical activity for the intervention group relative to the control group and subsequently improve cognitive and physical outcomes.

## **2. Introduction:**

### *2.1 Briefly describe the background and the importance of the research.*

The future of healthcare for older adults poses a unique problem for Singapore as our space constraints limits our ability in dealing with this issue and as Singapore's aging population is one of the fastest growing in Asia. Turning to technology and self-management seems necessary and research has to gather pace to look into the efficacy of programs with such aspects.

Physical frailty often interacts with cognitive decline (Boyle, et al., 2010; Furtado, et al., 2018; Panza, et.al., 2018) amongst this population. The term cognitive frailty was conceptualised to reconcile the associations (Furtado, et.al., 2018) and overlaps that the 2 concepts, Dementia and physical frailty had. It is defined as having both physical frailty and cognitive impairment that does not satisfy criteria for Major Neurocognitive Disorder (Kelaiditi, et al., 2013).

Adding the cognitive component to the definition of frailty have enhanced the predictive validity of adverse health outcomes (Kelaiditi, et. al., 2013) such as an increased prevalent rate of functional disability and mortality risks (Feng, et. al., 2017). With cognitive frailty representing an elevated risk for morbidity, it is crucial to look into interventions that could help slow older adult's arrival at this stage. One possible intervention is the promotion of physical exercise — which has been found effective in preventing and protecting against physical frailty and cognitive deterioration (Blondell et al., 2014; Kidd, et al., 2019; Losa-Reyna, et al., 2019; Sofi, et. al., 2010). There are also promising findings of the potential reversibility of cognitive decline. RCT studies show that aerobic physical activity had an impact on cognitive function among people with Alzheimer's Disease (Jia, et al., 2019) or Dementia in general (Groot, et al., 2016).

With increasing physical activity proving to be a potential method for delaying the onset or worsening of cognitive frailty, technology such as smart watches and mobile phone applications could represent a foray into such preventive intervention. Using tele-health devices to encourage positive health behaviours have been experimented with more in recent times (Thilarajah, et al., 2016; Wang, et. al., 2015). The step towards self-management and technology can complement and ease the burden on the future healthcare system. However, even with the current pervasiveness of wearable sensors and mobile phones in our daily lives, capabilities of such technology in healthcare interventions have yet to be widely validated. Thus, the usability and efficacy of such technologies are still unclear.

### 3. Preliminary Studies:

*3.1 Provide a brief account of the Principal Investigator's preliminary/pilot studies (if any) pertinent to the application. Please note that the IRB approval granted for this study will not cover preliminary/pilot studies that have already been conducted or are ongoing.*

This research is intended to be a feasibility study into the effectiveness of technology such as smart watches and mobile phone application in the lives and well-being of older adults. No preliminary/pilot studies were done prior to this.

However, participants will be recruited from an ongoing elderly cohort study (Community Health and Intergenerational study) also under the Principal Investigator of this study. That study is collecting biological, psychological and social health determinants of community-dwelling elderly in Singapore.

### 4. Methodology:

*4.1 Describe in detail the (i) experimental design and research procedures, (ii) research visits by the research subject (frequency and duration of procedures involved) and (iii) period of recruitment to accomplish the aims of this research.*

(i) This pilot study will be a randomized control trial with pre and post testing. Participants will either be randomly assigned to the intervention group or to the control group. The independent variable explored in the study is the use of the wearable technology and mobile application prompts while the levels of physical and cognitive improvements are the dependent measures. Additionally, the mediating variable measured is the levels of physical activity to ensure that proposed outcome measures are affected through an increased level of physical activity encouraged by the use of the device.

60 older adults aged 60 to 85 years old who are pre-frail with MCI will be recruited for this study. They will be recruited from an ongoing elderly cohort study, the Community Health and Intergenerational (CHI) study at the NUS Mind-Science Center. Since our study intends to encourage physical activity through wearable technology and mobile applications among those who have low activity and are at risk for cognitive and physical decline, older adults who are physically very active or have medical contraindications will be excluded.

Participants in the intervention group will be given the wearables which they will use together with the accompanying mobile application for the period of the study. During the period of intervention, the wearable will track the physical

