Baseline information on their personal demographics, neurocognitive data, physical activity and physical frailty will be collected. Level of physical activity is measured using objective data from the smart watch and the International Physical Activity Questionnaire (IPAQ) which collects information on hours of vigorous and moderate physical activity, walking and sitting by the participant in the last 7 days. The FRAIL questionnaire, a simple screening test for frailty in many elderly community samples, hand grip strength, Gait speed, Timed Up and Go (TUG) and a portion of the Short Physical Performance Battery (SPPB) will be used to measure physical frailty. A test battery of NCA that was used in the CHI study will be administered. This includes various commonly used measures of cognition: Rey Auditory Verbal Learning Test (RAVLT), Digit Span Forward and Backward (DS), Colour Trails Test (CTT), Wechsler's Block Design (WBS) and Semantic Verbal Fluency – Animals (SFA). In the event that social distancing measures due to COVID-19 are still in place, the Cambridge Neuropsychological Test Automated Battery (CANTAB) will be used to assess cognitive outcome instead. It is a computerized cognitive test, useful for tracking cognitive changes over time.

Follow up assessments of both cognitive and physical outcomes will be done at 3 months and 6 months. Follow up assessments allow us to test the sustainability of this intervention and to rule out novelty effects. Secondary variables such as sleep quality, levels of motivation, anxiety and depression will be included in the data collection. The questionnaires used are Pittsburgh Sleep Quality Index (PSQI), Barriers Self-Efficacy Scale (BARSE), Geriatric Depression Scale (GDS) and Geriatric Anxiety Inventory (GAI).

(ii) In all, participants will have to make 3 research visits and their entire participation will last 6 months.

|  |            |          |
|--|------------|----------|
|  | Procedures | Duration |
|--|------------|----------|

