Given a hypothesized treatment effect size of 0.4 according to previous similar studies, it was estimated using G\*Power that a total sample size of 42 was required to detect a significant within-between interaction with a power of .80 (assuming  $\alpha = .05$ ; correlation between repeated measures = .50; nonsphericity correction = 1). After considering for potential drop-out rates and publication value, a total sample size of N=60 was reached. Given that our valid sample size (N = 60) is larger than 42, our sample size is more than adequate to detect an effect size of 0.4 or larger, at a power of .80 if such effect exists.

The intervention outcomes will be analysed using repeated measures analysis of variance (ANOVA) and linear mixed models.

4.4 *What are the reasonably foreseeable risks, discomforts or inconveniences to a living research subject arising from this biomedical research and/or removal of tissue? Please also*

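### No primary outcome is named among ten or eleven cognitive and physical measures, while the sample size holds for one test of one unnamed outcome

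*Protocol*

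**What the plan says.** The abstract and section 4.1(i) define the outcomes as a group: "the levels of physical and cognitive improvements are the dependent measures". Physical activity is assigned the role of mediator.

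Section 4.1 then lists the instruments. The cognitive battery is "Rey Auditory Verbal Learning Test (RAVLT), Digit Span Forward and Backward (DS), Colour Trails Test (CTT), Wechsler's Block Design (WBS) and Semantic Verbal Fluency" (animals). The physical frailty measures are "The FRAIL questionnaire, a simple screening test for frailty in many elderly community samples", together with "hand grip strength, Gait speed, Timed Up and Go (TUG) and a portion of the Short Physical Performance Battery (SPPB) will be used". If COVID-19 distancing is still in force, CANTAB replaces the cognitive battery, and no CANTAB score is named.

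One lower tier is set apart: "Secondary variables such as sleep quality, levels of motivation, anxiety and depression will be included in the data collection". No measure, domain score or composite is called primary.

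Section 4.3 begins "Given a hypothesized treatment effect size of 0.4 according to previous similar studies" and concludes that "a total sample size of 42 was required to detect a significant within-between interaction with a power of .80", with alpha .05 and "correlation between repeated measures = .50; nonsphericity correction = 1". It raises the total to 60 and judges that number ample. It does not say which outcome the calculation is for. The analysis is repeated measures ANOVA and linear mixed models.

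**The concern.** The protocol does rank its measures: activity is the mediator, and sleep, motivation, anxiety and depression are secondary. Everything else stays on one undifferentiated main tier of ten or eleven measures. The power statement covers one test at .05 on one of them, without saying which.

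Two things follow. First, the assurance that 60 participants suffice cannot be checked against a particular outcome, because the assumed effect size is attached to none. Second, nothing prevents the measure that carries the conclusion from being chosen after the results are known, out of about ten tests each run at .05. In that case .05 would not be the error rate of the trial's conclusion.

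**Working it through.** **Inputs from the protocol.** Two arms (abstract). Three measurements: baseline, 3 and 6 months (abstract; visit table in 4.1). Effect size 0.4, alpha .05, power .80, correlation between repeated measures .50, nonsphericity correction 1 (4.3). Equal allocation is assumed, because the ratio is not stated. The metric of the 0.4 is not stated either.

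**Step 1: reproduce N=42.** For the G*Power within-between interaction with k groups and m measurements:

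- λ = f²·N·m/(1−ρ), df1 = (k−1)(m−1), df2 = (N−k)(m−1)
- Reading 0.4 as Cohen's d gives f = d/2 = .2. With k=2, m=3, ρ=.5 and N=42: λ = .04·42·3/.5 = 10.08, df = 2 and 80, critical F = 3.11, power .803.
- N=40 gives .78, so 42 is the smallest even total that reaches .80.
- Read as f = .4, the same formula needs only N=12. With two measurements and f = .2 it needs 52.

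The stated figure is therefore reproduced as one test of one outcome at .05. At N=60 (λ = 14.4, df 2 and 116) the power is .93.

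**Step 2: count the main-tier measures.** Cognitive: RAVLT, Digit Span, CTT, Block Design and verbal fluency, which is five, or six with Digit Span split. Physical: FRAIL, grip, gait speed, TUG and part of SPPB, which is five. The total is ten or eleven, taking one score per test. The count does not apply if CANTAB is used.

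**Step 3: chance of at least one false positive.** Assume no true effect on any measure and each test at two-sided .05. If the measures are independent this is 1 − .95^k: 1 − .95^10 = .401 and 1 − .95^11 = .431. For a common correlation r between outcomes, equicorrelated normal statistics were integrated numerically under three success rules. Each cell gives the result for ten / eleven measures.

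| Assumed r between outcomes | Any result, either direction | Any result favouring intervention | At least one cognitive and one physical, either direction |
|---|---|---|---|
| 0 | 40.1% / 43.1% | 22.4% / 24.3% | 5.1% / 6.0% |
| .3 | 35.1% / 37.5% | 17.8% / 19.1% | 6.7% / 7.5% |
| .5 | 28.7% / 30.4% | 14.4% / 15.2% | 7.9% / 8.7% |
| .7 | 21.3% / 22.3% | 10.7% / 11.2% | 8.4% / 9.0% |

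Simulating the 2-df interaction test itself gives similar values for the first column: 29.4% / 31.2% at r = .5 and 21.9% / 23.0% at r = .7. For a single two-sided test at .05, the benchmark is 5% in the first column and 2.5% in the second.

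The protocol gives no correlation between outcomes. The .50 in section 4.3 is between repeated measurements of the same outcome.

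**Step 4: power if the choice is made.** With the inputs of Step 1:

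- One primary at .05: .80 at N=42, .93 at N=60.
- Two primaries at .025 each: .71 at N=42, .88 at N=60, for each outcome.

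**The case against.** The strongest reply has four parts.

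*No success rule is stated.* A reader might infer that any one significant test would count as efficacy, so that the trial's false-positive rate for efficacy is 29-43%. The protocol does not support that. Section 1.1 states a chain: technology raises activity, and cognitive and physical outcomes then improve. A conjunctive reading is at least as close to that wording and gives about 5-9%. In addition, 29-43% counts results favouring control and stops at correlation .5, although several physical measures address the same construct. This part stands in full. The percentages are conditional illustrations and not properties of the plan.

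*It is a pilot.* The abstract and 4.1 call it a pilot and 3.1 a feasibility study, so strict familywise control over every measure would be out of proportion. This also stands, and it limits the remedy. It does not remove the point, because the protocol states an efficacy hypothesis and makes a formal power claim.

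*Multiplicity belongs in an SAP.* The adjustment method and composite scoring may well be set out there, and their absence here is no finding. The identity of the outcome to which N, alpha and power refer is different: it belongs next to the calculation in 4.3.

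*The power figure is still valid.* A reader might infer that N=42 and power .80 mean nothing. That goes too far: the calculation is correct for any single outcome with the assumed standardised effect. What is missing is the outcome for which that effect is being claimed.

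**Conclusion.** The point holds in a limited form. The protocol places ten or eleven cognitive and physical measures on one main tier with no primary outcome, and its sample size holds for one test of one of them, unnamed. That part rests on the text alone.

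The size of the consequence rests on assumptions. With every measure tested at .05, no true effects and any significant result read as support, at least one false positive in either direction has probability of about 40-43% under independence, 29-30% at correlation .5 and 21-23% at .7. For results favouring the intervention only, the range is about 11-24%. If both a cognitive and a physical result were required, it would be about 5-9%. This spread is itself the reason to fix the outcome in advance, since the protocol does not say which of these situations applies. The point is worth correcting but, in a pilot, does not call the design into question.

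**What to change.** In sections 4.1 and 4.3, before enrolment, do one of the following:

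- name one primary outcome, tested at .05 (power .80 at N=42 and .93 at N=60 under the plan's inputs); or
- name one cognitive and one physical primary, with alpha shared at .025 each (power .71 at N=42 and .88 at N=60).

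State that the G*Power calculation refers to that outcome or those outcomes. Define any cognitive primary so that it still works if CANTAB replaces the battery, for example by naming the corresponding CANTAB score in advance. A composite of the five listed tests alone could not be computed in that case. Label the remaining measures secondary or exploratory, in keeping with the pilot status.

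The change is to wording only and needs no new data or participants. Its one cost is a somewhat less favourable power figure if two primaries are chosen. At the planned 60 that figure stays above .80, but it falls below .80 if losses bring the analysed number down to 42.

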#### OFFICIAL USE ONLY

NUS-IRB Application Form (for HBR)

(IRB-FORM-H02)

activity of the older adults via the number of steps taken and number of hours of moderate physical work (based on heart rate). Heart rate and steps will be tracked whenever participants are wearing the watch, which is when they are awake. The watch is to be charged every night when they are sleeping. Participants will have to log down their physical activity by activating the physical activity tracker either on the watch or on the mobile application. If they did not hit the required level of physical activity, they will be sent a notification prompt through the mobile application with details of nearby workout locations as recommendation. For the control group, they will wear the wearables as a tracking device. No prompts will be given and the mobile application will only be installed but not used for this group.

The physical activity guidelines for participants will be 150 minutes of moderate intensity exercise in a week and 7500 steps daily. The technology's capability was developed in collaboration with students from Ngee Ann Polytechnic's School of Engineering. The wearable smart watch used will be the Fossil Smartwatch Sloan HR which enables tracking of the participant's heart rate and steps taken. Those in the intervention group will be able to view this information. However, the control group will not be able to obtain these information and their smart watches will be modified to only show them the time. The mobile application will be linked to the smart watches that participants wear. Participants have to own an Android phone which can support at least a version 6.0 Operating System. The application is meant to be a form of tracking and encouragement of physical activity for those in the intervention group. It will provide reminders in the form of push notifications if participants fail to reach their target for levels of physical activity. Two prompts – once at mid-day and once in the evening – will be sent out if target steps are not reached. Another prompt will be sent out in the middle of the week if target moderate intensity exercises are not reached. Those in the control group will not be receiving the reminders and notifications from the mobile application.

Baseline information on their personal demographics, neurocognitive data, physical activity and physical frailty will be collected. Level of physical activity is measured using objective data from the smart watch and the International Physical Activity Questionnaire (IPAQ) which collects information on hours of vigorous and moderate physical activity, walking and sitting by the participant in the last 7 days. The FRAIL questionnaire, a simple screening test for frailty in many elderly community samples, hand grip strength, Gait speed, Timed Up and Go (TUG) and a portion of the Short Physical Performance Battery (SPPB) will be used to measure physical frailty. A test battery of NCA that was used in the CHI study will be administered. This includes various commonly used measures of cognition: Rey Auditory Verbal Learning Test (RAVLT), Digit Span Forward and Backward (DS), Colour Trails Test (CTT), Wechsler's Block Design (WBS) and Semantic Verbal Fluency – Animals (SFA). In the event that social distancing measures due to COVID-19 are still in place, the Cambridge Neuropsychological Test Automated Battery (CANTAB) will be used to assess cognitive outcome instead. It is a computerized cognitive test, useful for tracking cognitive changes over time.

Follow up assessments of both cognitive and physical outcomes will be done at 3 months and 6 months. Follow up assessments allow us to test the sustainability of this intervention and to rule out novelty effects. Secondary variables such as sleep quality, levels of motivation, anxiety and depression will be included in the data collection. The questionnaires used are Pittsburgh Sleep Quality Index (PSQI), Barriers Self-Efficacy Scale (BARSE), Geriatric Depression Scale (GDS) and Geriatric Anxiety Inventory (GAI).

(ii) In all, participants will have to make 3 research visits and their entire participation will last 6 months.

|  |            |          |
|--|------------|----------|
|  | Procedures | Duration |
|--|------------|----------|

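### Watch-recorded activity depends on how long the watch is worn, and the reason to wear it differs by arm, so a raw comparison of watch totals can mistake unequal wear for unequal activity

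*Protocol*

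**What the plan says.** Section 4.1(i) measures activity on the watch by step count and by hours of moderate activity judged from heart rate. On when these are recorded it says: "Heart rate and steps will be tracked whenever participants are wearing the watch, which is when they are awake". The watch is charged overnight, so it has to be put back on each day for 6 months.

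The arms then differ in what the watch offers the wearer:

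- Intervention, on steps and heart rate: "Those in the intervention group will be able to view this information". This arm also gets prompts at mid-day, in the evening and mid-week when targets are missed.
- Control: "the control group will not be able to obtain these information and their smart watches will be modified to only show them the time". On prompts: "Those in the control group will not be receiving the reminders and notifications from the mobile application". On the app: "the mobile application will only be installed but not used for this group".

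Section 1.1 gives the first link of the hypothesis: "We hypothesize that technology will help increase engagement in physical activity for the intervention group relative to the control group". Section 4.1(i) makes activity the mediator through which the outcomes are meant to improve, and measures it with both the watch and IPAQ. The visit table in 4.1(ii) schedules IPAQ at all three visits. It places the handing out of watches at Visit 1, together with treatment allocation.

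**The concern.** An activity total from a wearable is the product of two things: how active the person is and how long the device is on the wrist. The protocol treats the second as fixed at waking time in both arms, yet its design gives the arms unequal reasons to wear the watch. An intervention participant gets feedback and prompts from it; a control participant gets a clock.

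If wear drifts apart over 6 months, raw step counts and moderate-activity hours drift apart with it, whatever the participants actually do. The watch is the objective measure of the mediator, so a wear artefact could be read as evidence that the technology raised activity. Passively recorded steps are affected as well as sessions that a participant has to start by hand, so setting aside the hand-started sessions would not remove the problem. Watches are issued at the allocation visit and no earlier run-in is described, so there is no watch baseline free of arm effects to adjust for.

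**Working it through.** **The plan's own figure.** The only power figure is a total of 42 in section 4.3 (effect size 0.4, power .80, α = .05, correlation .50, nonsphericity correction 1). Take k = 2 groups, m = 3 visits and 0.4 read as Cohen's d, so f = 0.2:

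- λ = f²·N·m/(1 − ρ) = 0.04 × 42 × 3 / 0.5 = 10.08
- df = (k − 1)(m − 1) = 2 and (N − k)(m − 1) = 80
- power = 0.803, so 42 is reproduced (f = 0.4 would need only 12)

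The wear point does not depend on this figure. It serves only to show that d = 0.4 is a fair yardstick.

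**How wear enters the total.** Recorded steps = steps per hour × worn hours. With equal true activity and steps spread evenly over the day, the ratio between arms equals the ratio of worn hours.

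Assumed figures, not in the protocol: 400 steps/h in both arms, 10 h of wear in control, 12 h in intervention.

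- Control: 400 × 10 = 4000
- Intervention: 400 × 12 = 4800
- Apparent increase: 800/4000 = 20%; true increase: 0
- The 800 steps are 800/7500 = 10.7% of the daily step target

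Reversed, the same wear gap hides a real effect. With a true 20% increase (480 steps/h) at 10 h of wear, intervention records 4800. Control at 400 steps/h and 12 h also records 4800.

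**Range.** Assumed: 15 waking hours, even accrual, 14 h of wear in intervention, SD of daily steps 2000–3000, 30 per arm (60 split 1:1), two-sided 5% test, no true difference. Apparent difference = true steps × (14 − control hours)/15.

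| True steps/day | Control wear | Apparent difference | d (SD 3000 to 2000) | Chance of a significant result |
|---|---|---|---|---|
| 7500 | 13 h | 500 | 0.17–0.25 | 9–16% |
| 7500 | 12 h | 1000 | 0.33–0.50 | 25–49% |
| 7500 | 10 h | 2000 | 0.67–1.00 | 73–97% |
| 5000 | 13 h | 333 | 0.11–0.17 | 6–9% |
| 5000 | 12 h | 667 | 0.22–0.33 | 14–25% |
| 5000 | 10 h | 1333 | 0.44–0.67 | 41–73% |

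The wear gap that alone yields d = 0.4 is 0.4 × SD × 15 / true steps. This runs from 0.4 × 2000 × 15/7500 = 1.6 h to 0.4 × 3000 × 15/5000 = 3.6 h per day.

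**Testing possible remedies on the 10 v 12 h example.**

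- Valid day defined as at least 10 worn hours: both arms qualify on every day, and 4000 v 4800 stands unchanged.
- Per worn hour: 4000/10 = 400 and 4800/12 = 400, so the false gap disappears.
- Limit of the per-hour rate: suppose every step falls in the 10 hours that controls wear the watch. Both arms then record 4000. The raw totals agree, but the rates are 400 v 4000/12 = 333, a false 17% deficit for intervention.

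No single summary is safe under every pattern of wear, so raw and wear-adjusted results need to be seen together.

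**The case against.** The strongest reply is that rules on valid days and wear time usually sit in a statistical analysis plan, which is not shown here. That is right as far as it goes: the absence of such a rule is not the point. What stands is that the protocol itself equates worn with awake and itself makes the incentive to wear the device differ by arm.

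The sentence on tracking can also be read as a wear instruction common to both arms, and section 9.1 provides for three-monthly review of adherence to the protocol. Both readings are fair. But an instruction does not secure equal compliance, and section 9.1 names no measure of wear.

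IPAQ does not depend on wear, so a watch effect without an IPAQ effect would be a visible warning. This limits the harm. IPAQ is, however, a 7-day self-report by people whose watch and app show them their arm, and the protocol gives neither measure precedence.

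A reader might infer three stronger things that the protocol does not support:

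- That it counts unworn hours as inactive. No section says so, and it prescribes no analysis that would rule out an adjustment for wear.
- That unequal wear must favour the intervention. Greater wear there is plausible, but repeated prompts could also put people off wearing the watch.
- That the trial's conclusions on outcomes are compromised. Cognition and physical performance are assessed at visits, and a wear artefact cannot create an effect on them.

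**Conclusion.** The point holds for the watch measure. A raw between-arm comparison of steps and moderate-activity hours is open to a measurement bias that the design makes possible, and that comparison feeds the first link of the hypothesis and the mediation reading. It does not directly touch the cognitive or physical performance outcomes, and it leaves IPAQ as a second, imperfect measure of activity.

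The size cannot be taken from the protocol. Under even accrual the relative error equals the relative difference in worn hours: 20% for 10 v 12 h. A gap of about 1.6 to 3.6 h a day would by itself produce d = 0.4. These figures rest on assumed step rates, waking hours and SDs, and they shrink if the unworn hours are quiet ones. The sign is unknown.

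**What to change.** In section 4.1(i), replace the assumption that worn equals awake with a measured quantity, and state how the watch data will be compared:

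1. Derive worn time from the heart-rate signal by one rule applied identically in both arms. This assumes that time-stamped heart rate is stored for controls even though it is hidden from them, which should be confirmed.
2. Report worn hours by arm and month. In a study that describes itself as a feasibility study, this is a useful result in its own right.
3. Compare steps and moderate activity with worn time accounted for, per worn hour or adjusted for worn hours, and show the raw totals beside them.
4. Show any minimum-hours restriction only as a sensitivity analysis. A threshold alone does not remove the bias, and it selects on behaviour after randomisation that may differ by arm.
5. Read the watch result alongside IPAQ before crediting the activity mechanism.

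The cost is a little more derivation work, with no added visits or devices. The drawback is that per-hour rates can themselves mislead if the watch is worn mainly during active hours, which is why both sets of results should be shown. Wear adjustment also does not settle differences in hand-started sessions, since "Participants will have to log down their physical activity by activating the physical activity tracker either on the watch or on the mobile application" and controls have a restricted watch and an unused app.
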